## Abstract

**Background:**

Adjustment problems and disorders are highly prevalent among university students worldwide. These problems can cause significant interference in academic and social functioning and increase vulnerability to other mental health disorders. Unfortunately, only half of students in need receive psychological help. Furthermore, few studies have evaluated psychological interventions for adjustment disorders in students. New, more scalable forms of treatment for students with an adjustment disorder need to be developed, evaluated, and implemented. The study aims to determine the effectiveness of an online transdiagnostic cognitive behavioural intervention for students experiencing adjustment disorder and to assess mediators of change.

**Method/design:**

In this three-arm randomized controlled trial, we plan to recruit 214 Polish students diagnosed with an adjustment disorder. Participants who meet initial eligibility criteria will be randomly assigned to one of three 6-week conditions: (1) online cognitive behavioural therapy intervention based on an existing, empirically supported transdiagnostic protocol, the unified protocol; (2) online progressive muscle relaxation training as an active control group; or (3) waiting-list control group. Both interventions are asynchronous, interactive, and include minimal amount of therapist support. Assessments will consist of self-report questionnaires, daily diary measures, and neurocognitive tasks for evaluating cognitive functioning. These will be conducted at baseline, post-treatment, and 1-month follow-up. Daily diary measures will be taken during the first and last week of treatment (or waitlist period). Primary outcome measures will include adjustment disorder severity; secondary outcome measures will consist of other negative (psychopathology: depression, anxiety, and stress) and positive (life satisfaction) indexes of mental health as well as process measures (e.g. mindfulness, experiential avoidance, cognitive fusion).

**Discussion:**

To our knowledge, the current study is the first to evaluate the effectiveness of a psychological intervention for students with adjustment disorder. Therefore, it may have important practical implications for students with this disorder. It can potentially guide the development of a scalable, validated treatment option.

**Trial registration:**

Clinical Trials, NCT05768308, registered 14 March 2023, https://www.clinicaltrials.gov/ct2/show/NCT05768308

## Introduction

Students face many developmental challenges when transitioning to a university setting, such as leaving the family home, becoming independent, and adjusting study habits for the university setting [1]. These challenges make them vulnerable to mental health problems, especially adjustment disorders. Research has shown that the prevalence of mental health problems in this group is higher than in the general population [2, 3].

Despite a clear need for mental health treatment, students rarely seek out and use in-person psychological services [4, 5]. Potential reasons for this include privacy concerns, low emotional openness, and financial issues [6]. Self-help online therapy programs can address many of these problems [7, 8]. They require fewer clinical resources and provide the possibility of help without fear of losing privacy. A survey conducted in 2020 in the USA showed that 71% of students would like to use this approach to treatment [9]. This proportion has continued to increase over time; in 2010, the percentage was only 58% [10]. Such interventions are currently used in the USA and a few countries worldwide; despite their promising effects, they are not widespread [11]. Unfortunately, no such intervention is available for students in Poland.

Adjustment disorder (AjD) is a disruption of adjustment following a stressful situation [12]. ICD-11 [13] lists revised criteria for disorders that require the presence of a psychosocial stressor and a stress reaction in the form of symptoms stemming from absorbing the stressor or its consequences, as well as clear disturbances in adaptation to the situation.

Several variables associated with AjD can be understood as transdiagnostic processes underlying theory of behavioural change in acceptance and commitment therapy (ACT). This includes psychological flexibility and inflexibility processes. Psychological inflexibility is understood as a failure to change one’s behaviour due to entanglement with inner experiences (e.g. thoughts and feelings), despite the detrimental or ineffective nature of the behaviour [14]. Inflexibility processes associated with AjD include experiential avoidance and cognitive fusion [15, 16]. The combination of these two processes has been found to play a significant role in causing and maintaining psychological distress [17, 18]. Also, negative repetitive thinking, which can be understood as a maladaptive experiential avoidance strategy, predicts psychological adjustment [19, 20].

On the other hand, psychological flexibility processes associated with AjD are mindfulness and self-compassion [21, 22]. They have been proposed to attenuate the effects of experiential avoidance and cognitive fusion on well-being (e.g. [23, 24]). Evaluating whether these variables are mechanisms of changes in psychological interventions aimed at AjD is essential.

Unfortunately, there is little research on AjD as a clinical diagnosis among students, and mental health among students is a relatively neglected area [1]. Previous studies have focused mainly on problems with academic adjustment, specifically, adjusting to new challenges connected to life at university. Results of these studies indicate that academic adjustment problems are highly prevalent (around 50%) and negatively impact students’ functioning, including worse grades, high university dropout rates, and poor mental health [25–29]. They are also associated with suicidal ideation [30, 31]. There is also a significant association between academic adjustment problems and the diagnosis of AjD [29].

Since the prevalence of academic adjustment problems is so high among this group and only half of students in need receive psychological help [32], it is important to develop and examine the effectiveness of an alternative—an online, self-help form of psychological assistance for students with AjD. It is also important to investigate the mechanisms of its effectiveness. Within the present literature on protecting students’ mental health, online therapy has been presented as an effective and potentially scalable solution [33]. To our knowledge, there has only been one study to date; it was focused on an online psychological intervention aimed at students with academic adjustment difficulties. It was based on an online meditation app available for commercial use. The study results suggest that individuals who used the app more frequently experienced more significant improvements in academic adjustment. Unfortunately, the study was limited by low app usage [34].

Internet interventions contain classic psychotherapy principles adapted to an online form. They can be fully automated—without psychotherapist support (unguided)—or allow therapist support [35]. They have been implemented worldwide for 20 years, but this area is still in its infancy in Poland [36], where there is a lack of both adapted e-interventions and research on their effectiveness [36]. Global data show that such programs can effectively treat mental disorders and be used in prevention efforts among student populations [37, 38].

Several studies have been published assessing the effectiveness of online therapeutic interventions aimed at people with AjD. All were based on CBT principles. Their promising results show small to medium effect-size improvements in experimental groups [39–42]. Unfortunately, these studies struggled with high dropout rates (50–80%) during the intervention. The percentage of people not helped by the interventions was also significant [43]. These studies relied on self-reported questionnaire methodologies, where it was impossible to determine any changes obtained in participants’ daily lives (at work, at school, or in family life). We intend to employ a more robust methodology and assess outcomes important for life in a university environment—such as cognitive functioning and academic performance. We will also study daily diary entries to increase the validity of results and obtain a more nuanced understanding of treatment effects.

Researchers have identified several factors that may improve the effectiveness of online psychotherapeutic interventions, such as interactive content, shorter intervals between sessions, and targeting the intervention to a specific type of stressor or a specific population [43, 44]. Several of these suggested changes will be incorporated into the intervention used in the present trial.

AjD is a disease with various clinical forms, with a predominance of depression, anxiety, or anger; therefore, transdiagnostic cognitive behavioural therapy (CBT) raises hope for increasing the effectiveness and clinical utility of treatment for this disorder. A study conducted among college students in 2013 confirmed that transdiagnostic CBT is an effective form of treatment for AjD [45]. The unified protocol (UP)—which will be used in the current study—is a structured, manualized transdiagnostic intervention for emotional disorders. The UP aims to address temperamental characteristics, particularly neuroticism and resulting emotion dysregulation, which are argued to be a common factor underlying all emotional disorders [46].

### Objectives

The main objective of the planned research is to evaluate the effectiveness of an online UP intervention among students experiencing AjD.

More specific objectives are as follows: (1) evaluate the effectiveness of the intervention relative to waiting-list and active control groups according to self-reported measures; (2) investigate the effectiveness of the intervention in the daily lives of participants; (3) assess the effectiveness of the intervention in the cognitive functioning of students; (4) conduct an examination of predictors and mediators of treatment response; (5) compare the impact of both treatment approaches, with different putative mechanisms of action, on outcome measures; and finally (6) evaluate the maintenance of AjD alleviation at 1-month follow-up.

## Methods/design

### Study design

This study is a parallel group randomized controlled trial (RCT). The participants will be allocated to one of three 6-week conditions: (1) online cognitive behavioural therapy, based on the unified protocol (iCBT-UP); (2) online progressive muscle relaxation training (iPMR, active control group); and (3) waiting-list control group (WLC). The last group will receive access to their chosen intervention after the waiting period (6 weeks). To help WLC participants maintain motivation, weekly emails will be sent to remind them of the study and to assess their mood. They will be instructed to contact the research team in instances of any crisis. At that point, they will be administrated by our team psychotherapist or psychiatrist and referred to an adequate service. Assessments will consist of questionnaires, a cognitive task and a study of daily diaries. All assessments will be administered through an online data collection platform delivered by organisers (Supporty.pl), occurring at (1) screening, (2) baseline (prior to randomization), (3) at the end of the 6-week online program (or waitlist period), and (4) 1 month after finishing treatment (for participants in the active intervention conditions). Daily diary studies will be carried out for entries in the first and again in the last week of the interventions. Cognitive task will be administered at baseline, at the end of 6 weeks of online intervention, and 1 month after finishing treatment. The study will follow SPIRIT guidelines (Standard Protocol Items: Recommendations for Interventional Trials) [47].

Figure 1 shows the trial design. The study protocol and informed consent have been approved by the Ethics in Research Committee of the Faculty of Psychology, University of Warsaw.

**Fig. 1 Fig1:**
[figure not shown]
Design of the trial

### Participant recruitment and inclusion and exclusion criteria

Participants will be recruited using announcements in popular social media and university newsletters. The study will be advertised to Polish students from different universities around the country. Interested participants will provide informed consent and then complete screening questionnaires. Those meeting preliminary eligibility criteria will then be assessed using the Mini-International Neuropsychiatric Interview (MINI) to ensure they meet Diagnostic and Statistical Manual of Mental Disorders, Fifth Edition (DSM-5) [48] diagnostic criteria for an AjD as a primary diagnosis and to establish comorbidities. The diagnostic interview will be administered by a trained psychologist or psychotherapist by video conference and then entered to the database.

The inclusion criteria consist of having student status, being 18 years old or older, having access to the internet and using a computer or smartphone, and meeting the diagnostic criteria of AjD in the IADQ questionnaire and meeting diagnostic criteria for AjD in the MINI.

The exclusion criteria consist primarily of conditions that require prioritization for immediate or simultaneous treatment: specifically, an increased risk of suicidality intent or ideation, bipolar and psychotic disorder, and/ or alcohol/substance use disorder. Individuals will also be excluded if they are receiving another psychological treatment at the start of the study or have no time to participate in the program. Pharmacological treatment during the intervention period will be allowed, provided that the type and dose of medication are stable for 6 weeks before study involvement.

Individuals not meeting the inclusion criteria will be referred to adequate services.

### Randomization and blinding

Subjects who meet the inclusion criteria will be randomized to one of two active groups or the waiting-list group using a 2:2:1 allocation ratio. The participants will be randomly allocated using a computerized block randomization, using block sizes of 6. Random allocation will be performed using an algorithm developed by a computer scientist and executed independently of the research team by an independent program [49]. The main researcher will then reveal the concealed allocation and inform participants of their placement into one of three groups. Randomization will be stratified based on the score of the initial AjD questionnaire assessment (the IADQ; see description below). The principal investigator responsible for determining study eligibility will be blinded to the randomization sequence. The researchers and psychotherapists leading the study and contacting participants cannot be blinded to allocation for practical reasons; however, those conducting the MINI evaluation will be blind to the condition allocation during the assessment.

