### Sample size calculation

The sample size was determined in relation to the between-group effect size and calculated using G*Power software. Previous research on an online UP intervention and online interventions for AjD has revealed a between-group effect size at the level of *d* = 0.5 and a within-group effect size at the level of *d* = 0.63 [42, 87]. Assuming an alpha 0.05 with a power of 0.80 and post-treatment between-group effect size of *d* = 0.5 (iCBT-UP versus control), 190 participants in the three groups will be sufficient to detect assumed differences. However, because the literature reveals dropout rates from online CBT interventions, with minimal guidance, of approximately 30% [88], a total sample of 247 participants will be recruited.

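### The stated 2:2:1 allocation and the stated block size of 6 cannot both be right, and the protocol does not show which one is wrong

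*Protocol article*

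**What the plan says.** All the allocation parameters are in the protocol article, under Randomization and blinding. Eligible students are "randomized to one of two active groups or the waiting-list group using a 2:2:1 allocation ratio". The next sentence reads: "The participants will be randomly allocated using a computerized block randomization, using block sizes of 6". The same paragraph adds "Randomization will be stratified based on the score of the initial AjD questionnaire assessment", so the blocks run within strata of the IADQ score. It gives no second block size and no rule by which composition changes from block to block. The Study design section confirms three arms ("The participants will be allocated to one of three 6-week conditions") and gives no other ratio.

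The Sample size calculation section sets out its assumptions ("Assuming an alpha 0.05 with a power of 0.80 and post-treatment between-group effect size of" d = 0.5, iCBT-UP versus control) and concludes that "190 participants in the three groups will be sufficient to detect assumed differences". After an allowance for dropout it arrives at 247 to be recruited. It states neither the ratio behind the 190 nor whether the test is one-sided or two-sided.

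**The concern.** Permuted-block randomisation keeps a ratio by filling every block in that ratio, so the block size has to be a multiple of the sum of the ratio terms. For 2:2:1 that sum is 5, and 6 is not a multiple of it. A programmer given these two sentences must change one of them or invent a scheme that the protocol does not describe.

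The ratio fixes the size of the waiting-list arm, and with it the precision of both comparisons of iCBT-UP with a control. The Objectives and the Discussion make both comparisons stated aims. If the wrong sentence is followed, the arm sizes differ from those planned, and this cannot be undone once participants are randomised.

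**Working it through.** **Inputs.** Ratio 2:2:1, block size 6 and stratification by IADQ score (Randomization and blinding); three arms (Study design); alpha 0.05, power 0.80, d = 0.5, 190 evaluable, 247 recruited (Sample size calculation). Assumption: sidedness is not stated, so both readings are shown.

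**1. Can a block of 6 hold 2:2:1?** The ratio sums to 2 + 2 + 1 = 5, and 6 mod 5 = 1.
- Slots needed: 6 × 2/5 = 2.4, 6 × 2/5 = 2.4, 6 × 1/5 = 1.2. These are not whole numbers.
- There are 10 ways to fill a block of 6 with at least one slot per arm: 2/2/2, the six orderings of 1/2/3, and the three orderings of 1/1/4. None is 2:2:1.
- The only one that treats the arms equally is 2/2/2, which is 1:1:1.
- Multiples of 5 do work: 5 gives 2/2/1, 10 gives 4/4/2, 15 gives 6/6/3.

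**2. Does the plan's own 190 show which ratio was meant?** Sample size for 80% power at d = 0.5, alpha 0.05:

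| Reading | Calculation | Total |
|---|---|---|
| Two-sided, 1:1:1 | 63 per arm (normal) or 63.8, so 64 (t-test); × 3 | 189 or 192 |
| One-sided, 2:2:1 | waiting list 37.6, so 38; 76 + 76 + 38 | 190 |
| Two-sided, 2:2:1 | waiting list 47.7, so 48; × 5 | 240 |
| One-sided, 1:1:1 | 50.2, so 51 per arm; × 3 | 153 |

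The 190 is reproduced exactly by one-sided 2:2:1 and closely by two-sided 1:1:1. It does not settle the ratio.

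**3. Arm sizes.**
- At 247 randomised: 2:2:1 gives 247 × 0.4 = 98.8, 98.8 and 247 × 0.2 = 49.4. 1:1:1 gives 247 / 3 = 82.3 per arm. The waiting-list arm differs by about 33.
- The Abstract gives 214 instead of 247. On that figure the waiting-list arm is 214 × 0.2 = 42.8 or 214 / 3 = 71.3.

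**4. Power at the plan's 190 evaluable.** Two-sample t-test with noncentrality d × √(n₁n₂ / (n₁ + n₂)).
- 2:2:1, iCBT-UP 76 against waiting list 38: 0.5 × √(2888 / 114) = 2.52.
- 2:2:1, iCBT-UP 76 against iPMR 76: 0.5 × √38 = 3.08.
- 1:1:1, 63.3 against 63.3, either control: 0.5 × √31.67 = 2.81.

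| Contrast | Sidedness | 2:2:1 | 1:1:1 |
|---|---|---|---|
| iCBT-UP vs waiting list | two-sided | 0.70 | 0.80 |
| iCBT-UP vs waiting list | one-sided | 0.80 | 0.88 |
| iCBT-UP vs iPMR | two-sided | 0.86 | 0.80 |
| iCBT-UP vs iPMR | one-sided | 0.92 | 0.88 |

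**The case against.** **Blocks of 6 could still average 2:2:1.** Five blocks of varying composition can total 12/12/6 in 30 participants, and the algorithm itself is not shown. This is true, so it cannot be said that the program fails or has delivered another ratio. But the text describes no such scheme, no single block would be 2:2:1, and stratification splits the sequence into shorter lists that are more likely to stop mid-cycle. A misprint in one of the two sentences is at least as plausible. The text needs correcting in either case.

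**Any fixed ratio gives a valid randomised comparison.** This stands. The contradiction does not by itself bias the treatment effect; what is uncertain is arm size and precision.

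**The power figures do not measure damage from the block size.** This also stands. The lower power against the waiting list belongs to 2:2:1 itself, and blocks of 2/2/2 would raise it. The figures show only what depends on the choice of ratio. They also rest on a simple t-test, whereas the Data analysis section plans hierarchical linear modelling by intention to treat with multiple imputation.

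**Predictable allocations.** A reader might infer from the single fixed block size, and from the sentence "The main researcher will then reveal the concealed allocation and inform participants of their placement into one of three groups", that the last allocation in every block can be deduced, and might put the count at 247 / 6, about 41. The document does not support this. Deducing a slot requires a known block composition, which is exactly what the text fails to fix, and a running tally within each IADQ stratum. The same section also has the allocation run by a program independent of the research team, and the principal investigator who determines eligibility is blinded to the sequence. A fixed, published block size in an open-label trial remains a minor weakness, with no count attached.

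**Conclusion.** The two adjacent sentences contradict each other as a matter of arithmetic, and nothing elsewhere in the protocol reconciles them. One must be corrected; the document does not show which. A block of 6 points to 1:1:1, while the exact 76 + 76 + 38 = 190 points to 2:2:1 with a one-sided test, but both are inferences.

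What depends on it is a waiting-list arm of about 49 or about 82 at 247 randomised, and a difference of 0.08 to 0.10 in power for iCBT-UP against the waiting list at 190 evaluable. If 2:2:1 is kept with a two-sided test, 190 evaluable give 0.70 for that contrast and miss the stated 0.80. These power figures assume d = 0.5, alpha 0.05 and a two-sample t-test.

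This must be fixed, because a stated randomisation rule cannot be carried out as written. The conclusion rests on the contradiction alone. It does not claim a biased comparison, a failed randomisation or a given number of predictable allocations.

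**What to change.** - Reconcile the two sentences under Randomization and blinding. Either keep 2:2:1 and use block sizes that are multiples of 5 within each IADQ stratum, or state 1:1:1 with multiples of 3 (6 then works).
- Under Sample size calculation, state the ratio and the sidedness, and align the sample size and power with them.
- Recruitment was due to start on 1 November 2023. If an allocation list already exists, check the sequence actually generated against the corrected text and report it.
- As a minor addition, vary the block size at random and keep it from recruiting staff, for example 5 and 10 under 2:2:1.

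The cost is one protocol sentence, one parameter in the randomisation program and a matching edit to the sample size section. If 2:2:1 is kept with a two-sided test and 0.80 power against the waiting list, the evaluable total rises from 190 to 240. Larger or varied blocks allow slightly more imbalance at the end of each list.

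### One fixed, published block size in a trial led by unblinded researchers leaves some upcoming allocations open to inference, and blinding the eligibility decision to the sequence alone does not prevent it

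*Protocol article*

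**What the plan says.** All of the following is in the protocol article, mainly under Randomization and blinding.

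- **Method:** participants are allocated "using a 2:2:1 allocation ratio" and "using a computerized block randomization, using block sizes of 6", stratified by the screening IADQ score. The number of strata and their cut-offs are not given.
- **Execution:** the allocation is "executed independently of the research team by an independent program".
- **Disclosure:** "The main researcher will then reveal the concealed allocation and inform participants of their placement into one of three groups".
- **Eligibility:** "The principal investigator responsible for determining study eligibility will be blinded to the randomization sequence".
- **Team:** "The researchers and psychotherapists leading the study and contacting participants cannot be blinded to allocation for practical reasons".
- **Raters:** "those conducting the MINI evaluation will be blind to the condition allocation during the assessment".

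Three other sections bear on this. Participant recruitment and inclusion and exclusion criteria excludes, among others, people who "have no time to participate in the program", with no threshold. Governance and oversight of the trial places the principal investigator in a three-role management group that oversees recruitment and meets weekly in the active phase. Trial status plans recruitment from 1 November 2023 to 1 March 2024, so earlier allocations can be known while later candidates are still being assessed.

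**The concern.** Allocation concealment requires that whoever admits a participant cannot foresee that participant's arm. Blinding to the sequence hides the list. It does not hide what follows from allocations already disclosed plus a known block make-up. Under a fixed block size the last place in every block is determined, and the places before it are partly determined. Nothing stated keeps the eligibility decision away from allocations already revealed.

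A person who could foresee an arm would have two levers: how strictly a judgement-based criterion such as available time is applied, and when a candidate is entered. The arms differ in appeal, since the waiting list delays access by six weeks. If entry were steered, the arms would differ at baseline in ways that adjustment removes only in part. The primary outcome, the IADQ, is a self-report questionnaire, so the analysis could not be relied on to repair this.

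**Working it through.** **Inputs.** Ratio 2:2:1 and block size 6 (Randomization and blinding); recruitment target 247 (Sample size calculation); 214 in the Abstract.

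**Step 1: does the printed block fit the ratio?** 6 × 2/5 = 2.4, 6 × 2/5 = 2.4 and 6 × 1/5 = 1.2. It does not; only multiples of 5 fit. This is a separate contradiction, but it leaves the block make-up unknown. The check is therefore run for a block of 5 (2,2,1), for a block of 6 read as (2,2,2), and for a fixed block of 10 (4,4,2).

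**Step 2: the observer.** Assume someone who knows the block make-up and every earlier allocation in the stratum. An allocation is certain when only one arm remains in the block. The expected number of certain places per block is 1 + P(last two alike) + P(last three alike) + ….

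- (2,2,1): P(last two alike) = (2×1 + 2×1)/(5×4) = 0.20, so 1.20/5 = **24.0%**.
- (2,2,2): P(last two alike) = 3×(2×1)/(6×5) = 0.20, so 1.20/6 = **20.0%**.
- (4,4,2): 1 + 26/90 + 48/720 + 48/5040 = 1.365, so 1.365/10 = **13.7%**.

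**Step 3: best guess.** The observer names the arm with most places left. Averaging the chance of being right over places:

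- (2,2,1): (0.400 + 0.500 + 0.533 + 0.600 + 1)/5 = 3.033/5 = **60.7%**, against 40% without blocks.
- (2,2,2): (0.333 + 0.400 + 0.500 + 0.533 + 0.600 + 1)/6 = 3.367/6 = **56.1%**, against 33.3%.
- (4,4,2): **55.9%** by the same recursion, against 40%.

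**Step 4: waiting list already used up.**

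- (2,2,1): the single waiting-list place falls on average third of five, so 2/5 = **40%** of places come after it.
- (2,2,2): the later of two places falls on average at 2×7/3 = 4.67 of six, so 1.33/6 = **22%** come after it.

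**Step 5: in participants, as a ceiling.** 247 × 0.20 = 49 and 247 × 0.24 = 59. With the Abstract's 214: 43 to 51.

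**Step 6: effect of varying the block size.** Blocks of 5 and 10 were mixed at random with equal probability, for an observer who knows both sizes and all earlier allocations (simulation, 400 runs of 100 participants).

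| Scheme | Certain in advance | Best guess right |
|---|---|---|
| Fixed 5 (2,2,1) | 24.0% | 60.7% |
| Fixed 6 (2,2,2) | 20.0% | 56.1% |
| Fixed 10 (4,4,2) | 13.7% | 55.9% |
| Random 5 or 10 | about 7% | about 57% |

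Varying the size removes most of the certainty but little of the advantage in guessing.

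**The case against.** The strongest reply is that the key link is not in the text. The article uses two labels, the main researcher who discloses and the principal investigator who decides eligibility. A reader might infer that they are one person, or that the principal investigator sees each allocation. The article says neither. The management group oversees recruitment, but nothing says that allocations are tabled there. An article may also leave delegation of roles to the full protocol. This stands, and the point is limited accordingly. It rests on what is stated: a fixed printed block size, disclosure by a team member, unblinded study leaders, and an eligibility decider whose only stated protection is not seeing the sequence.

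Second, there are real safeguards. Independent execution protects the list. The MINI raters are blind to condition, and the diagnostic judgement is theirs. Risk management words the suicidality exclusion more categorically than the criteria section does, and lack of time would usually be reported by the applicant. Discretion is therefore narrow. But neither safeguard covers the final eligibility decision or the timing of entry. Table 3 schedules the MINI only at enrolment, before that person has an allocation, so the raters' blinding does not address allocations already made to others.

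Third, a reader might take 49 to 59 as the number of allocations that would be known. The documents do not support that as an expectation. It requires knowledge of the make-up, the block boundaries, the strata, every earlier allocation and who comes next. The printed 6 does not reveal a make-up that fits 2:2:1. At 247 over about 121 days, roughly two people a day would be randomised, so several candidates may be in progress at once. All of this pulls the figure down.

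**Conclusion.** The point holds as a weakness of a stated design rule. Blinding to the sequence does not by itself conceal upcoming allocations when the block size is fixed and in print and the team leading the trial knows past allocations. The size is a worst-case ceiling of 20% (2,2,2) to 24% (2,2,1) of allocations certain in advance, for an observer who knows the block make-up and all earlier allocations in the stratum. The real figure could be far lower. Stratification slows the inference but does not stop it, because the IADQ score is known from screening.

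A reader might go further and call this selection bias. The documents show an opportunity only: they give no evidence that anyone would use it, and any motive to spare a student the waiting list is conjecture. The weakness does not depend on how the mismatch between 6 and 2:2:1 is settled, since every fixed-block reading tested leaves some allocations certain. It is worth correcting because the correction is cheap and steered entry could not be fully repaired in the analysis.

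**What to change.** Make three changes together in Randomization and blinding and in the platform settings:

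1. Have the independent program vary block sizes at random among multiples that fit the stated ratio (for 2:2:1, for example 5 and 10), and keep the sizes out of any document the recruiting team sees.
2. Have the platform lock the signed eligibility decision, covering every criterion, and the completed baseline before it accepts a randomisation request. This would also settle the order of events: Study design puts baseline before randomisation, while Table 3 lists allocation before baseline.
3. Withhold the running allocation list from whoever decides eligibility, and say so.

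The first change is not enough alone, since best guesses fall only from 61% to about 57%. Having the platform rather than the main researcher send the allocation message would add little, because the team is in weekly contact with participants.

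The cost is a settings change and a few sentences. The downside is a slightly larger possible imbalance within strata.
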